We will test the hypothesis that intervention participation as a whole improves the probability of being in employment subject to social insurance contributions 12 months after study entry in comparison to a group of the same population that receives treatment as usual (TAU) within the German social security system. Furthermore, we will test the effectiveness of intervention participation in terms of secondary outcomes that relate to (re-)employment, health and well-being, social integration, help-seeking intentions and behaviors, self-stigma, and utilization of health services within the health care system. Overall, we will test whether intervention participation is associated with more favorable outcomes than non-participation. More specifically, the following nine hypotheses are proposed:

*Hypothesis 1:* Twelve months after study entry (t1), participants in the intervention group will be significantly more likely to be in employment subject to social insurance contributions than participants in the control group.*Hypothesis 2: *Twelve months after study entry (t1), participants in the intervention group will have been significantly more days in employment subject to social insurance contributions than participants in the control group (H2a). For those that will have started such employment within 12 months after study entry (t1), the number of days until starting the first employment contract subject to social insurance contributions after study entry is significantly lower in the intervention group than in the control group (H2b).*Hypothesis 3:* Eighteen months after study entry (t2), participants in the intervention group will be significantly more likely to be in employment subject to social insurance contributions than participants in the control group.*Hypothesis 4: *Twenty-four months after study entry, participants in the intervention group will be significantly less likely to having been transferred to long-term basic income support than participants in the control group (long-term basic income support

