= at least 21 months in basic income support within the preceding 24 months).*Hypothesis 5: *Twelve months after study entry (t1), participants in the intervention group will report significantly higher levels of job-search self-efficacy than participants in the control group.*Hypothesis 6: *Twelve months after study entry (t1), participants in the intervention group will report significantly more favorable outcomes on various psychosocial measures (i.e., psychological distress, health-related quality of life, general health state, somatic symptom burden, depressive symptoms, symptoms of anxiety, social integration, self-stigma) in comparison to participants in the control group.*Hypothesis 7: *Twelve months after study entry (t1), participants in the intervention group will report significantly higher intentions to and past acts of seeking professional help for mental health issues than participants in the control group.*Hypothesis 8: *Eighteen months after study entry (t2), participants in the intervention group will report significantly more favorable outcomes on the secondary outcomes mentioned in Hypotheses 5-7 than participants in the control group.*Hypothesis 9: *Of those job center clients that complete the screening measure for psychological distress, at least 30% will report experiencing at least moderate psychological distress indicated by a score of nine or greater on Kessler’s Psychological Distress Scale – K6 version [58].^1^

Furthermore, to evaluate the feasibility, implementation, and sustainability of the intervention components as regular service in job centers, we will conduct qualitative interviews with relevant stakeholders (e.g., job center executive board members, employment advisors, intervention providers, and intervention participants). Finally, we will evaluate the cost effectiveness of the 3for1-intervention program.

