### Inclusion and exclusion criteria

Participants will be included in the study if they fulfill the following inclusion criteria: (1) currently registered client at one of the collaborating job centers; (2) aged 18 to 60 years; (3) having received full basic income support based on Germany’s Second Book of the Social Code (i.e., *Arbeitslosengeld II* until December 2022 or *Bürgergeld* starting January 2023) up to a maximum of six months at time of study entry, or having received partial basic income support to top up income from employment subject to social insurance contributions for longer than six months, but having switched to full basic income support within the last six months due to recent job loss; (4) experiencing at least moderate psychological distress indicated by a score of nine or greater on *Kessler’s Psychological Distress Scale* – K6 version (range: 0–24) [58];^2^ (5) wish to obtain employment subject to social insurance contributions (i.e., competitive employment in the primary labor market); (6) willingness to participate in all parts of the study, including participation in the data collection and intervention participation (if offered as part of the IG); and (7) written informed consent to participate.

Participants will be excluded from the study based on (1) not fulfilling the inclusion criteria; (2) insufficient knowledge of German; and (3) currently being in employment subject to social insurance contributions or being self-employed for at least 15 working hours per week.

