Upon study entry, research staff will record detailed contact information from participants as well as their banking details for compensation, including written consent to use these details for said purpose. Subsequently, research staff will conduct an entry interview with participants and ask them to complete a questionnaire (i.e., baseline assessment, t0). After completing this baseline assessment, participants will be contacted for a short telephone interview after six months to assess health service utilization in the preceding six months, as well as after 12 months (i.e., t1) and 18 months (i.e., t2) for more in-depth assessment similar to the baseline assessment, including conducting an interview and completing a questionnaire. Additionally, research staff will ask participants’ written consent to request certain data from their job center records, specifically their status of receiving basic income support benefits (yes vs. no) and the duration of receiving full basic income support at 12, 18 and 24 months after study entry. Whether written consent for this additional data request is given or not will not affect study participation.

Figure 1 shows a flow chart for participants’ study experience.

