As part of the t1 online questionnaire, we will ask IG participants to evaluate their intervention experience. We will first ask them to rate their overall satisfaction with the intervention on a visual analogue scale, ranging from 0 (= *lowest satisfaction*) to 100 (= *highest satisfaction*). Secondly, IG participants will be asked to rate their satisfaction with the intervention components in which they have participated in the intervention phase. For this rating, we adapt a questionnaire for client satisfaction with hospital stays (ZUF-8) [94] to fit our intervention components. Satisfaction with each intervention component will be evaluated with eight items; each item offering four response options. Thirdly, we will apply seven self-created items for each component to evaluate to which extent the components are considered helpful by participants for different aspects of their life (e.g., to change their situation, to find employment, to improve mental health). Each item will be rated in a 5-point Likert scale from 1 (= *strongly disagree*) to 5 (= *strongly agree*).

Additionally, we will assess health service utilization every six months with the *Client Socio-Demographic and Service Receipt Inventory* (CSSRI) [95] (German version: [96]) in order to evaluate the cost effectiveness of the 3for1-intervention program. The CSSRI will be completed via structured interviews, either as part of the interviews at t0, t1 and t2 or an additional interview six months after study entry.

In addition to the questionnaires and structured interviews, we will inquire data from job center records whether participants receive full basic income support benefits and for how many months they have received full benefits since study entry at 12, 18 and 24 months after study entry.

Finally, we will record the intensity of IG participants’ intervention utilization in our database: Intervention providers will record contact times (in minutes) with participants after every intervention session, including an overview of discussed topics. Based on these recorded contact times, we will calculate overall intervention utilization intensity as well as intervention component utilization intensity to explore whether more intensive utilization of the intervention and its components is associated with its effectiveness.

An overview of enrollment, intervention, and assessments across the different measurement points is given in Table 2.

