**Job center records:**						
Receiving benefits: yes vs. no				X	X	X
Duration of receiving benefits after study entry (in months)				X	X	X

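### Hypothesis 4 counts months in basic income support, but the records requested give months of full support only, so topped-up employment can be scored as having left long-term support

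*Protocol article*

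**What the plan says.** All references are to the protocol article.

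- **Objectives, Hypothesis 4.** At 24 months, "participants in the intervention group will be significantly less likely to having been transferred to long-term basic income support than participants in the control group". That state is defined as "at least 21 months in basic income support within the preceding 24 months". Neither phrase is limited to full support.
- **Inclusion and exclusion criteria, criterion 3.** The article separates full from partial support and describes the second route into the trial as "having received partial basic income support to top up income from employment subject to social insurance contributions". In the article's own terms, then, a wage top-up is a form of basic income support.
- **Participant recruitment and timeline.** Subject to a separate written consent, the record request has a status item, given as "their status of receiving basic income support benefits (yes vs. no". Its duration item is worded as "the duration of receiving full basic income support at 12, 18 and 24 months after study entry". The status item is unqualified; the duration item is restricted to full support.
- **Secondary outcomes.** The request is described again, with the status item given as "whether participants receive full basic income support benefits". Here the duration item is worded as "for how many months they have received full benefits since study entry at 12, 18 and 24 months after study entry". In this section both items are restricted to full support.
- **Table 2, job center records.** The duration row reads "Duration of receiving benefits after study entry (in months", with neither full nor partial specified.

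No section asks for months of partial support.

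**The concern.** The definition and its data source measure different things. Someone who takes a low-paid or part-time job and keeps a top-up remains in basic income support but stops accumulating months of full support. On the definition as written, that person can be in long-term support; on the data described, the same person is a success.

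This scoring error needs a job, and the intervention is meant to produce jobs. The error may therefore be unequal between the groups. At stake is what a favorable result on Hypothesis 4 would mean: that more people left the benefit system, or that more people moved from full to partial support. The second may be worth reporting, but it is not what the hypothesis claims.

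**Working it through.** **The plan's own figures.** No sample size or effect size is stated for Hypothesis 4. The figures in Sample size concern the primary outcome and reproduce. With 15% and 30%, two-sided alpha 0.05, power 0.90, pooled variance and no continuity correction:

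n = [1.960 × √(2 × 0.225 × 0.775) + 1.282 × √(0.15 × 0.85 + 0.30 × 0.70)]² / 0.15² ≈ 161 per group

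161 / (1 − 0.35) = 247.7, so 248 per group. These figures are correct and have no bearing on this point.

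**Who is scored differently.** Let F be months of full support and P months of partial support in the 24 months after entry.

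- Definition as written, if any support counts: long-term when F + P ≥ 21.
- Data as described: long-term when F ≥ 21.
- The two disagree when F ≤ 20 but F + P ≥ 21.

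Example: F = 20 and P = 4 gives F + P = 24. This person is long-term on the definition and not long-term on the data. With F = 21 and P = 3 the two agree. So only top-up spells that bring full support below 21 months matter; a short or late topped-up job changes nothing. Yes/no status at 12, 18 and 24 months cannot rebuild a 21-of-24-month count.

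**Possible size (illustration).** Inputs:

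- 15% of the control group (CG) and 30% of the intervention group (IG) have F ≤ 20. These are the planning rates for employment at 12 months, borrowed here as an assumption.
- A share s of them stays on partial support, so that F + P ≥ 21. The article gives no value; 20% to 50% is assumed.

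Scored on full support, the long-term rates are 85% (CG) and 70% (IG), a difference of 15.0 points whatever s is. Scored on any support, with the same s in both groups, the difference is (0.30 − 0.15) × (1 − s):

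| s | CG long-term | IG long-term | Any-support difference | Full-only difference | Excess |
|---|---|---|---|---|---|
| 20% | 88.0% | 76.0% | 12.0 points | 15.0 points | 3.0 points |
| 50% | 92.5% | 85.0% | 7.5 points | 15.0 points | 7.5 points |

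**Direction.** With separate shares, the shift is 0.30 × s_IG − 0.15 × s_CG.

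- It is zero when s_CG = 2 × s_IG. With 50% and 25%: 0.075 − 0.075 = 0.
- It favors the control group above that ratio. With s_CG = 50% and s_IG = 10%: 0.030 − 0.075 = −4.5 points.
- If the groups have equal rates of leaving full support and equal s, it is zero.

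In general the shift equals the difference between the groups in the proportion with topped-up employment long enough to matter.

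**The case against.** The strongest reply is that Hypothesis 4 was always meant as full support. Both descriptions of the duration data say full. Criterion 3 admits people with more than six months of partial support provided that they moved to full support within the last six months, so the trial's benefit clock at entry already ignores partial months. On that reading nobody is misclassified and a single word is missing. This reading is plausible and the article does not rule it out. It changes the remedy but does not remove the defect: the definition as written is unqualified, and a reader of the results would take it to mean leaving basic income support.

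A second reply is that an analysis plan can settle the definition. It can settle the meaning, but it cannot supply partial-support months that were never requested. The interviews collect job dates, hours and net income, but they are not described as recording months of benefit, and the last one is at 18 months.

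Three stronger readings are tempting and are not supported:

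- **That Hypothesis 4 is biased toward the intervention.** This depends on the intended meaning and on top-up shares in each group, which the article does not give. The shift can be zero or reversed.
- **That the mismatch would create an effect where none exists.** On the illustration's own inputs, 50% to 80% of those leaving full support also leave top-up, so a real difference of 7.5 to 12.0 points is enlarged.
- **That the welfare-state cost analysis would overstate savings.** Statistical methods does not say which data field feeds that analysis, nor that partial payments are valued at zero.

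**Conclusion.** The inconsistency is real and visible in the text. The outcome in Hypothesis 4 cannot be computed as stated from the data described, and the yes/no status item is itself defined in two ways. The effect on Hypothesis 4 is conditional. If any support counts, if employment differs as planned and if equal shares of 20% to 50% in both groups stay on top-up, the apparent benefit would exceed the true one by 3.0 to 7.5 points. That range rests on an assumed top-up share and on 12-month employment rates standing in for cumulative months over 24, so it shows the possible scale and is not an estimate. The point should be corrected because it decides what Hypothesis 4 can conclude. It concerns one secondary outcome; the primary analysis and the sample size are unaffected.

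**What to change.** Choose one of two routes and state it in the protocol.

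1. **Keep the broad definition.** Request months of partial support in addition to months of full support at 12, 18 and 24 months, and score Hypothesis 4 on months of any support. The cost is one more field in an existing record request and possibly an amendment to the consent wording.
2. **Narrow the definition.** Restate Hypothesis 4 as at least 21 months of full basic income support in the preceding 24, and do not interpret the result as leaving basic income support. This is a wording change and costs nothing in data collection.

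Under either route, use the same terms for duration and for yes/no status in Objectives, Participant recruitment and timeline, Secondary outcomes and Table 2.

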## Methods

### Design and setting

This multi-center study is designed as a non-randomized controlled trial, with participants being allocated to either an intervention group (IG) or passive control group (CG). The group allocation is time-based, that is, there will be a first recruitment period during which all interested individuals will be allocated to the CG, followed by a second recruitment period during which all participants will be allocated to the IG.

Both groups will receive TAU in the collaborating job centers, with IG participants additionally having access to the 3for1-intervention, including its three components: (1) short-term psychotherapy, (2) IPS-based job coaching, and (3) peer support. The study will be conducted on behalf of the Jobcenter Ulm (main funding recipient and study sponsor) at the Ulm University Medical Center and the University Hospital Tübingen in collaboration with six job centers in Southern Germany. This trial was registered with the German Clinical Trials Register on 11 May 2022 (DRKS00029002).

### Inclusion and exclusion criteria

Participants will be included in the study if they fulfill the following inclusion criteria: (1) currently registered client at one of the collaborating job centers; (2) aged 18 to 60 years; (3) having received full basic income support based on Germany’s Second Book of the Social Code (i.e., *Arbeitslosengeld II* until December 2022 or *Bürgergeld* starting January 2023) up to a maximum of six months at time of study entry, or having received partial basic income support to top up income from employment subject to social insurance contributions for longer than six months, but having switched to full basic income support within the last six months due to recent job loss; (4) experiencing at least moderate psychological distress indicated by a score of nine or greater on *Kessler’s Psychological Distress Scale* – K6 version (range: 0–24) [58];^2^ (5) wish to obtain employment subject to social insurance contributions (i.e., competitive employment in the primary labor market); (6) willingness to participate in all parts of the study, including participation in the data collection and intervention participation (if offered as part of the IG); and (7) written informed consent to participate.

Participants will be excluded from the study based on (1) not fulfilling the inclusion criteria; (2) insufficient knowledge of German; and (3) currently being in employment subject to social insurance contributions or being self-employed for at least 15 working hours per week.

### Participant recruitment and timeline

Potential participants will be recruited via the employment advisors in the collaborating job centers. They will check their clients’ basic eligibility to participate in the study (i.e., inclusion criteria 1 to 3) and introduce the study’s generic premise and purpose to eligible clients during one of their first appointments in the job center. If eligible job center clients are interested and willing, they will be given the K6 to complete as a screening for their level of psychological distress. Subsequently, the employment advisors score their responses and, if they score nine or greater (i.e., inclusion criterion 4), they will be referred to the research staff located at the job center. If job center clients do not score nine or greater on the K6 and/or do not want to participate in the study, they will be asked permission to forward contact details to research staff to be contacted again in two to three months’ time to re-assess interest and/or eligibility to participate in the study (if inclusion criteria 1 to 3 are still fulfilled). Employment advisors will receive training for introducing the study to potential participants, scoring the K6 and referring participants with a K6-score of nine or greater to research staff.

Potential participants who fulfill inclusion criteria 1 to 4 will have an appointment with research staff who will inform them verbally and in writing about the study’s premise, objectives and timeline and what study participation would entail. Furthermore, they will receive information regarding the voluntary nature of their participation, data protection regulations as well as compensation for their time and travel costs. They will be given sufficient time to consider their participation and opportunity to ask questions. Subsequently, if participants remain interested, research staff will clarify whether potential participants wish to obtain employment and are willing to participate in all parts of the study (i.e., inclusion criteria 5 and 6), and, finally, obtain written consent of participants (inclusion criterion 7).

Upon study entry, research staff will record detailed contact information from participants as well as their banking details for compensation, including written consent to use these details for said purpose. Subsequently, research staff will conduct an entry interview with participants and ask them to complete a questionnaire (i.e., baseline assessment, t0). After completing this baseline assessment, participants will be contacted for a short telephone interview after six months to assess health service utilization in the preceding six months, as well as after 12 months (i.e., t1) and 18 months (i.e., t2) for more in-depth assessment similar to the baseline assessment, including conducting an interview and completing a questionnaire. Additionally, research staff will ask participants’ written consent to request certain data from their job center records, specifically their status of receiving basic income support benefits (yes vs. no) and the duration of receiving full basic income support at 12, 18 and 24 months after study entry. Whether written consent for this additional data request is given or not will not affect study participation.

Figure 1 shows a flow chart for participants’ study experience.

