#### Secondary outcomes

Secondary outcomes encompass variables in relation to (re-)employment, health and well-being, social integration, help-seeking, and self-stigma. These variables will be assessed at t0, t1 and t2 by self-report, predominantly via online questionnaires, but also as part of structured interviews.

We will collect data on various variables related to (re-)employment. We will apply a one-item measure to ask participants about their *motivation to perform paid work* in the primary labor market [20], ranging from 1 (= *low*) to 3 (= *stron*g), with 4 (= *not applicable*,* as currently employed*) specifically for assessment at t1 and t2. Additionally, we will measure how confident participants feel in finding a job, namely job-search self-efficacy (JSSE). Variables regarding current employment status will be measured as self-report at t1 and t2 only (as the inclusion criteria at t0 preclude current employment). More specifically, participants will be asked in the exit and follow-up interview about employment they have started since entering the study or since the exit interview respectively. These questions encompass start and end date of potential employment, type of employment (e.g., part- or full-time employment, self-employment), working hours per week and average monthly net income. Finally, participants will also be asked about measures taken to obtain re-employment since the last assessment.

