**ENROLLMENT:**						
**Eligibility screen (incl. psychological distress)**	X					
**Project information**	X					
**Informed consent **	X					
**Allocation**^******^	X					

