**ASSESSMENTS:**						
**Questionnaires:**						
Sociodemographic variables		X		X	X	
Motivation to work		X		X	X	
Job-search self-efficacy (JSSE)		X		X	X	
Psychological distress (K6)				X	X	
Health-related quality of life (EQ-5D)		X		X	X	
General health state (EQ-VAS)		X		X	X	
General well-being (WHO-5)		X		X	X	
Somatic symptom burden (SSS-8)		X		X	X	
Depressive symptoms (PHQ-9)		X		X	X	
Symptoms of anxiety (GAD-7)		X		X	X	
Mental health diagnoses		X		X	X	
Mental health treatment		X		X	X	
Social outcomes (SIX)		X		X	X	
Social inclusion (ESIS)		X		X	X	
Help-seeking (GHSQ; AHSQ)		X		X	X	
Self-stigma (SSMIS-SF)		X		X	X	
Intervention evaluation (IG only)				X		

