**Database records (IG only):**						
Intervention utilization intensity (in minutes)				X		
Intervention component utilization intensity (in minutes)				X		

^*^t0: Enrollment and baseline assessment at the same timepoint, individual intervention period of 12 months for IG starting directly afterward; t1: exit interview and questionnaires 12 months after enrollment and baseline, and, for IG, directly after end of intervention period; t2: follow-up interview and questionnaires 18 months after enrollment and baseline, and, for IG, 6 months after end of intervention period

^**^Allocation based on enrollment timing in study: allocation of the first cohort to CG and the second cohort to IG

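### The only pre-treatment K6 is the eligibility screen, whose consequence differs by recruitment period; the K6 part of H6 and H8 should also be adjusted for the t0 PHQ-9 and GAD-7

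*Protocol article*

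**What the plan says.** **Eligibility (Inclusion and exclusion criteria).** Entry requires "experiencing at least moderate psychological distress indicated by a score of nine or greater on" the K6, which runs from 0 to 24.

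**Screening (Participant recruitment and timeline).** Clients fill in the K6 at the job center. "Subsequently, the employment advisors score their responses and, if they score nine or greater (i.e., inclusion criterion 4), they will be referred" to research staff. Clients below nine may, with their permission, be re-contacted after two to three months. Advisors are trained in scoring. The article mentions no independent re-scoring.

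**Timing (Table 2).** The pre-treatment measure appears only in the enrollment row "Eligibility screen (incl. psychological distress"). In the questionnaire block, the row "Psychological distress (K6") is marked at t1 and t2 only. PHQ-9, GAD-7, SSS-8, WHO-5 and the other outcome scales are all marked at baseline. The section on secondary outcomes says: "These variables will be assessed at t0, t1 and t2 by self-report, predominantly via online questionnaires". The table footnote adds: "t0: Enrollment and baseline assessment at the same timepoint".

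**Allocation (Design and setting).** "there will be a first recruitment period during which all interested individuals will be allocated to the CG", and the intervention group (IG) follows. Both groups get usual care, "with IG participants additionally having access to the 3for1-intervention, including its three components".

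**Analysis (Objectives; Statistical methods).** Psychological distress is the first measure listed in H6, and H8 carries it to 18 months. Continuous outcomes are compared by ANCOVA. The K6 covariate is not named.

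**The concern.** One score does two jobs. It decides entry, and it is the only K6 available as a baseline for the K6 comparison. Allocation follows the calendar, so staff can know at screening what a score of nine will open. The Discussion gives advisors' cooperation with the programme, and the change it may bring to job-center practice, as the reason for having no parallel control group. The same change could reach the screening step.

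If reported or scored distress were higher in the intervention period, IG participants would start from inflated values and fall back further by t1. An ANCOVA on the inflated value reads part of that fall as a programme effect. At stake is a false benefit on the scale that defines the target population.

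**Working it through.** **Plan's own figure.** The article gives no figure for the K6 comparison. Its sample size for the primary outcome reproduces. For 15% v 30%, two-sided 0.05 and power 0.90: n = [1.960·√(2·0.225·0.775) + 1.282·√(0.15·0.85 + 0.30·0.70)]² / 0.15² = 160.8, so 161 per group; 161/0.65 = 247.7, so 248. Nothing below depends on this, except that 250 × 0.65 leaves about 162 per group at t1.

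**Assumptions, none of them in the article.** Clients' K6 mean 8 or 10, SD 5; reliability of one K6 0.70 or 0.85; 12-month correlation of true scores 0.7; no treatment effect; entry at nine or more. IG-period screens are either raised uniformly by 0, 1 or 2 points, or only near-misses (8, or 7 to 8) are lifted to nine.

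**Formula.** ANCOVA difference = (difference in t1 means) − slope × (difference in screening means), IG minus control. Negative values favor IG.

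- *Uniform 1 point, mean 8, reliability 0.70.* The t1 difference is −0.30 and the difference in change is −0.66, so the screening difference is −0.30 + 0.66 = 0.36. With slope 0.48: −0.30 − 0.48 × 0.36 = −0.47.
- *Uniform 1 point, mean 10, reliability 0.85.* The t1 difference is −0.32 and the difference in change is −0.77, so the screening difference is 0.45. With slope 0.59: −0.32 − 0.59 × 0.45 = −0.59.
- *Scores of 7 to 8 lifted to nine, mean 8, reliability 0.85.* The t1 difference is −0.71 and the difference in change is +0.14, so the screening difference is −0.85. With slope 0.62: −0.71 + 0.62 × 0.85 = −0.18.

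| IG-period screening | ANCOVA difference | Type I error |
|---|---|---|
| Same as control period | about 0.00 | 0.050 |
| Uniform +1 | −0.47 to −0.59 | 0.17 to 0.26 |
| Uniform +2 | −0.96 to −1.18 | 0.51 to 0.76 |
| Near-misses lifted to nine | −0.05 to −0.18 | 0.05 to 0.07 |

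In the first row the control mean falls by 1.3 to 2.2 points through regression to the mean, and the comparison stays unbiased because both groups fall alike. Over a wider set of assumptions, lifting scores of 7 to 8 gave 0.03 to 0.21 points.

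**Which covariate helps.**

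- *Replacing the screen, uniform 1-point shift.* A fresh t0 K6 leaves about 0.1 point. A PHQ-9-type covariate, assumed to correlate 0.8 with true distress, leaves 0.13 to 0.20.
- *Replacing the screen, near-miss lifting.* Replacement can do harm. With true mean 8, SD 4.5 and reliability 0.8, a fresh K6 leaves 0.12 (8 lifted) and 0.22 (7 to 8 lifted), against 0.07 and 0.18 with the screening score.
- *Adding PHQ-9 and GAD-7 to the screening K6.* The false difference was smaller in every shift scenario run, for example 0.57 to 0.35 (uniform) and 0.18 to 0.11 (near-miss), with slightly smaller standard errors. The gain depends on how closely the two scales follow true distress, which the article does not give.

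**The case against.** The case for leaving this alone is substantial.

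- **Timing text.** A reader might infer that the secondary-outcomes section promises a second K6 at baseline, which Table 2 then omits. The footnote treats enrollment and baseline as one timepoint, so the screen counts as the t0 K6 and the two places agree.
- **Truncation.** A reader might infer that a score cut at nine biases the comparison by itself. It does not: with equal screening the difference is about zero.
- **Opportunity.** Clients answer the K6 themselves after hearing only a general introduction, trained advisors add up six items, and re-contact runs through research staff. Control entry also brings compensation for time and travel. An incentive at a cut-off mainly gives reason to lift near-misses, where the adjusted bias is under half a standard error (0.18 against 0.42). The article also gives no basis for supposing that repeat-screen entries were commoner in one period.
- **Covariate.** It is not named, and may properly be left to the analysis plan.
- **Remedy.** The baseline questionnaire follows full information about participation, so it too can be answered differently by group.

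All of this stands. It limits the size and certainty of the point. It does not remove the fact that the screening score is the only K6 candidate for the covariate, nor the sensitivity of the result if scores shifted across their range.

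**Conclusion.** The point holds as a vulnerability that the design leaves open, and the article does not show that a bias occurred. The K6 comparisons in H6 and H8 have one pre-treatment K6, tied to eligibility, whose consequence differs by period. If intervention-period scores ran higher, ANCOVA on that score alone would give a false benefit of about 0.5 to 0.6 points per 1-point uniform shift, or about 0.03 to 0.21 points if only scores of 7 to 8 are lifted. Both figures rest on the assumed K6 distribution, reliability and stability above, and on the screening score being the covariate.

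A reader might extend this to the primary outcome or to all of H6 and H8. The article does not support that: employment is not analyzed on a K6 baseline, and the other scales have their own t0 values. Any effect of screening on who enters the groups is a separate matter, and the Discussion already concedes that the groups may differ at baseline.

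**What to change.** 1. In the K6 analyses at t1 and t2, name as covariates the screening K6 together with the t0 PHQ-9 and GAD-7, which both groups complete at the research-staff baseline.
2. Add a sensitivity analysis with PHQ-9 and GAD-7 in place of the screening K6. Read it beside the first, since replacement helps under a uniform shift but often not under near-miss lifting.
3. Report by recruitment period the distribution of screening scores around nine and the number who entered on a repeat screen.
4. State in Table 2 or its footnote that the screening score is the t0 K6.
5. Use a separate t0 K6 as covariate only if both groups have one. With t1 expected to be complete in June 2025, enrollment would have ended about 12 months earlier, and controls were recruited first. An item added late could not cover both groups.

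The cost is a few lines in the analysis text and one descriptive table, with no new PHQ-9 or GAD-7 data. Item 3 needs the screening scores and repeat-screen status to have been kept.
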